## Abstract

**Background:**

Some symptomatic degenerative conditions of the lumbar spine may be treated with spinal fusion if conservative treatment has failed. The minimally invasive technique of transforaminal lumbar interbody fusion (MIS TLIF) is increasingly used but has been found to generate increased radiation exposure to the patient and staff. Modern three-dimensional (3D) C-arm devices are capable of providing conventional two-dimensional fluoroscopic images (x-rays) as well as 3D image sets for intraoperative navigation. This study was designed to compare the radiation exposure between these two intraoperative imaging techniques in MIS TLIF procedures.

**Methods:**

This study is a randomized controlled trial. Forty participants scheduled to undergo monosegmental MIS TLIF will be recruited and randomly allocated to one of two groups with respect to the applied intraoperative imaging technique: conventional fluoroscopy (FLUORO group) and 3D fluoroscopy-based navigation combined with conventional fluoroscopy (NAV group). Furthermore, patients scheduled to undergo bisegmental MIS TLIF during the recruitment period for monosegmental MIS TLIF will be assessed for eligibility and will be randomly assigned separately. The primary endpoint is the radiation exposure to the surgeon and is measured by dosimeter readings. Secondary endpoints are the radiation exposure to the assistant surgeon, scrub nurse, anesthetist, patient, and C-arm as well as radiation exposure in relation to the body mass index of the patient.

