## Background

Lumbar spinal fusion is used to treat a variety of symptomatic degenerative deformities and instabilities [1]. The traditional open surgical technique includes a long skin incision with dissection and retraction of paravertebral muscles, thereby exposing the bony structures of the posterior spine. In 2003, Foley *et al.* [2] first described a minimally invasive technique for transforaminal lumbar interbody fusion (MIS TLIF) using tubular retractors under fluoroscopic guidance. A recent meta-analysis showed that MIS TLIF resulted in less blood loss and shorter hospital stay but increased x-ray exposure time compared with the open TLIF technique [3]. Modern three-dimensional (3D) C-arm devices are capable of providing conventional two-dimensional (2D) fluoroscopic images (x-rays) as well as 3D image sets for intraoperative navigation [4,5]. The main principle of intraoperative C-arm-based 3D imaging is an automated orbital rotation of the C-arm around the patient who has already been draped and positioned on the operating table. During this rotational scan, a 3D image data set is obtained from multiple successive 2D fluoroscopic images [4,5]. The 3D scan is performed after the staff has left the operating room. Additionally using navigated instruments and a navigation device, the surgeon can then perform accurate screw placement without additional radiation exposure.

The radiation exposures of MIS TLIF procedures using conventional 2D fluoroscopic images and 3D fluoroscopy-based navigation have not been systematically compared so far. Thus, the purpose of this study is to compare the radiation exposure to the surgeon, assistant surgeon, scrub nurse, anesthetist, and patient in monosegmental and bisegmental MIS TLIF using conventional fluoroscopy (FLUORO group) and 3D fluoroscopy-based navigation (NAV group) as intraoperative imaging techniques.

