### Randomization to treatment groups

Participants will be randomly assigned by using ‘RITA - Randomization In Treatment Arms’ computer software (StatSol, Sereetz, Germany). Participants were randomly assigned in permuted blocks of four and six, according to computer-generated random numbers, to undergo MIS TLIF using either conventional fluoroscopy (FLUORO group) or 3D fluoroscopy-based navigation (NAV group). Separate randomization files are created for monosegmental and bisegmental MIS TLIF. The randomization software ensures that the treatment allocation cannot be viewed prior to randomization and cannot be changed after randomization.

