### Data collection

In this study, the primary endpoint is the radiation exposure to the surgeon during monosegmental MIS TLIFs in the FLUORO and NAV groups. The secondary endpoints are the radiation exposures to the assistant surgeon, scrub nurse, anesthetist, patient, and C-arm as well as radiation exposure in relation to the body mass index of the patient in the FLUORO and NAV groups.

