#### Statistical analysis

The primary endpoint (radiation exposure to the surgeon) will be tested at the 0.05 level. Results will be expressed as means with standard deviations. Analysis of independent continuous quantitative variables between groups will be performed by using the two-tailed Student’s *t* test. Pearson’s correlation test will be used to determine correlations between two variables. Statistical comparisons for categorical values between groups will be performed by using the two-tailed Fisher exact test. Prism 6 for Mac (GraphPad Software Inc., La Jolla, CA, USA) will be used as statistical software.

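### Secondary endpoints are not tied to a fusion level, bisegmental surgeon exposure is no listed endpoint, and the stated t test ignores the level by which patients are randomised

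*Protocol article*

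**What the plan says.** - **Purpose.** The Background section sets out to compare exposure to surgeon, other staff and patient "in monosegmental and bisegmental MIS TLIF using conventional fluoroscopy (FLUORO group" and the navigation arm. The Design section also names both levels, and Table 1 makes both eligible.
- **Recruitment.** In the Abstract, "patients scheduled to undergo bisegmental MIS TLIF during the recruitment period for monosegmental MIS TLIF will be assessed for eligibility"; their allocation is described there as separate from that of the monosegmental cases. The Sample size section gives 17 per group, with a target of 20, for monosegmental procedures only. There is no bisegmental target.
- **Randomisation.** "Separate randomization files are created for monosegmental and bisegmental MIS TLIF", in permuted blocks of four and six (Randomization to treatment groups).
- **Primary endpoint.** "the primary endpoint is the radiation exposure to the surgeon during monosegmental MIS TLIFs in the FLUORO and NAV groups" (Data collection). The Abstract gives the primary endpoint without the level.
- **Secondary endpoints.** "The secondary endpoints are the radiation exposures to the assistant surgeon, scrub nurse, anesthetist, patient, and C-arm", together with exposure in relation to body mass index (Data collection). They are defined for the two imaging groups, with no fusion level named.
- **Analysis.** "Analysis of independent continuous quantitative variables between groups will be performed by using the two-tailed Student" t test (Statistical analysis). Pearson correlation and Fisher's exact test are the only other methods, and none is linked to fusion level.

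**The concern.** These statements do not fit together in three respects.

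1. Bisegmental patients are consented and randomised to serve a stated purpose whose lead outcome is surgeon exposure. That outcome in those patients is neither a primary nor a secondary endpoint.
2. The level restriction is written into the primary endpoint and dropped in the next sentence. A reader cannot tell whether a secondary comparison covers monosegmental cases, both levels separately, or everyone.
3. The trial randomises by level, but the stated test does not use level.

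The choice between these readings could therefore be made after the data are seen. If all patients in each arm are compared directly, the dose difference between one-level and two-level surgery goes into the error term. If bisegmental cases are tested alone in small numbers, a non-significant result could be taken as evidence that navigation brings no reduction in two-level surgery. The Abstract's Discussion promises recommendations on the use of the two techniques, so either outcome could reach practice.

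**Working it through.** **1. The plan's own figures (Sample size section).**
- FLUORO: 266 × 55.75 / 101.4 = 146.2 μSv. NAV: 12 × 1.1 × 266 / 101.4 = 34.6 μSv. Both agree with the text.
- Planning means are 150 and 50 μSv, a difference of 100 μSv; alpha is 0.05 two-sided and power 0.80. No SD is stated, so n = 17 cannot be reproduced from the stated inputs alone.
- Solving backwards with the exact t test, n = 17 per group needs an SD of about 98 to 101 μSv. The implied standardised difference is about 100/100 = 1.0. At that value power is 0.807 with 17 per arm and 0.869 with 20.

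**2. Cost of ignoring level in a comparison over both levels.** Set the within-level SD to 1. Let b be the bisegmental patients per arm, added to 20 monosegmental, and δ the mean difference between levels in SD units, taken as equal in both arms. With p = b/(20 + b), the SD within an arm when level is ignored is √(1 + p(1 − p)δ²). The documents give neither b nor δ; both are assumed.

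| b per arm | p(1 − p) | δ = 1.0 | δ = 1.5 |
|---|---|---|---|
| 4 | (4/24)(20/24) = 0.139 | √1.139 = 1.067 | √1.3125 = 1.146 |
| 8 | (8/28)(20/28) = 0.204 | √1.204 = 1.097 | √1.459 = 1.208 |

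The error SD is inflated by about 7% to 21%.

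**3. What this does to the added patients.** Assume equal within-level SD and the same treatment effect in both levels. Relative to 20 monosegmental patients per arm, a level-stratified analysis multiplies the standard error by √(20/24) = 0.913 (b = 4) or √(20/28) = 0.845 (b = 8). Ignoring level gives:
- b = 4: 0.913 × 1.067 = 0.974, or 0.913 × 1.146 = 1.046.
- b = 8: 0.845 × 1.097 = 0.927, or 0.845 × 1.208 = 1.021.

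So the unstratified standard error lies between about 7% smaller and 5% larger than with monosegmental patients alone. Much or all of the gain is lost.

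**4. Confounding by level.** With blocks of four and six in separate files, the arms can differ by at most 3 patients within a level, and only if accrual stops mid-block. Take an extreme case of 7 against 4 bisegmental patients with 20 monosegmental per arm. The bisegmental shares are 7/27 = 0.259 and 4/24 = 0.167, a difference of 0.093. The contrast shifts by 0.093 × 1.0 = 0.09 SD to 0.093 × 1.5 = 0.14 SD, in a chance direction, against an implied effect of about 1 SD. This is small and not systematic.

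**5. Bisegmental cases alone.** Carrying over the standardised difference of 1.0 (an assumption), exact t power is 0.223, 0.286, 0.461 and 0.562 with 4, 5, 8 and 10 per arm. At 10 per arm, keeping the 100 μSv difference, it is 0.81 with an SD of 75 μSv and 0.29 with 150 μSv. The difference detectable with 80% power is 2.02 SD at 5 per arm and 1.32 SD at 10.

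**The case against.** The strongest reply is that the plan has a clear hierarchy. Monosegmental surgery is the primary and powered population, and the bisegmental cohort is an addition. A non-primary cohort without a sample-size target is legitimate. Separate randomisation suggests separate comparisons, and no section says the levels will be pooled. The article condenses a fuller protocol, so details of stratification may stand there. The bisegmental numbers, the level difference and the carried-over effect size are all assumed.

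Most of this stands, and it rules out two stronger readings that a reader might infer.
- *The bisegmental part of the purpose cannot be answered.* This does not follow. Separate randomisation gives a valid bisegmental comparison; only its precision is unplanned, and that could turn out poor or adequate.
- *The secondary analyses pool the levels.* The text does not say so. Pooling is the literal reading of secondary endpoints defined for the two groups, combined with a t test between groups, and separate analysis is equally compatible with it.

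The reply does not remove the mismatch within the article. The level is stated for one endpoint and omitted for the others, and the purpose's lead outcome is missing for one randomised cohort. Those are statements the article itself makes about endpoints, not detail left to another document.

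**Conclusion.** The point holds as a mismatch between purpose, endpoints and stated analysis. The primary comparison and its sample size are unaffected. If secondary endpoints are compared over all patients with the stated test, the loss is mainly precision: an error SD about 7% to 21% larger, resting on an assumed level difference of 1 to 1.5 SD and 4 to 8 bisegmental patients per arm. Confounding by level is not a material problem, given separate blocked files. The power of a bisegmental comparison alone is unknown, since the article gives neither a number of patients nor an SD; the figures above are illustrations. A single common NAV-to-FLUORO ratio across levels is one possible model, but the point does not require it.

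**What to change.** - Keep the primary endpoint as it is, restricted to monosegmental procedures.
- List surgeon exposure in bisegmental procedures as a secondary endpoint.
- State that every secondary endpoint is analysed within each level, and that any comparison including both levels has level (one or two) as a stratification factor.
- State that the bisegmental comparison has no planned sample size. Report it as an estimate with a 95% confidence interval, and draw no conclusion of no difference from a non-significant result.

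The cost is a few sentences in the Data collection and Statistical analysis sections, using a factor that the randomisation already creates. No further patients, dosimeters or procedures are needed. The one concession is that the bisegmental part of the purpose is openly presented as estimation.

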**Discussion:**

Results of this randomized study will help to compare the radiation exposure to the operating staff and patient during MIS TLIF procedures using conventional fluoroscopy versus 3D fluoroscopy-based navigation combined with conventional fluoroscopy. Furthermore, recommendations regarding the appropriate use of the investigated intraoperative imaging techniques will be made to improve radiation protection and to reduce radiation exposure.

**Trial registration:**

Registration number of the German Clinical Trials Register: DRKS00004514. Registration date: 11 August 2012.

## Background

Lumbar spinal fusion is used to treat a variety of symptomatic degenerative deformities and instabilities [1]. The traditional open surgical technique includes a long skin incision with dissection and retraction of paravertebral muscles, thereby exposing the bony structures of the posterior spine. In 2003, Foley *et al.* [2] first described a minimally invasive technique for transforaminal lumbar interbody fusion (MIS TLIF) using tubular retractors under fluoroscopic guidance. A recent meta-analysis showed that MIS TLIF resulted in less blood loss and shorter hospital stay but increased x-ray exposure time compared with the open TLIF technique [3]. Modern three-dimensional (3D) C-arm devices are capable of providing conventional two-dimensional (2D) fluoroscopic images (x-rays) as well as 3D image sets for intraoperative navigation [4,5]. The main principle of intraoperative C-arm-based 3D imaging is an automated orbital rotation of the C-arm around the patient who has already been draped and positioned on the operating table. During this rotational scan, a 3D image data set is obtained from multiple successive 2D fluoroscopic images [4,5]. The 3D scan is performed after the staff has left the operating room. Additionally using navigated instruments and a navigation device, the surgeon can then perform accurate screw placement without additional radiation exposure.

The radiation exposures of MIS TLIF procedures using conventional 2D fluoroscopic images and 3D fluoroscopy-based navigation have not been systematically compared so far. Thus, the purpose of this study is to compare the radiation exposure to the surgeon, assistant surgeon, scrub nurse, anesthetist, and patient in monosegmental and bisegmental MIS TLIF using conventional fluoroscopy (FLUORO group) and 3D fluoroscopy-based navigation (NAV group) as intraoperative imaging techniques.

## Methods

### Design

This study is a randomized controlled trial to assess the intraoperative radiation exposure during monosegmental and bisegmental MIS TLIF procedures to the surgeon, assistant surgeon, scrub nurse, anesthetist, and patient. The patients are preoperatively randomly assigned to one of two intraoperative imaging groups that will be used for pedicle screw placement: conventional fluoroscopy (FLUORO group) and 3D fluoroscopy-based navigation (NAV group).

### Study population

This study will focus on patients who are at least 18 years old and who have an indication for a monosegmental or bisegmental MIS TLIF procedure within L2 and S1 because of degenerative disc disease (as opposed to infectious, neoplastic, or traumatic causes).

### Inclusion and exclusion criteria

Entry inclusion and exclusion criteria (Table 1) were developed with the goal of maximizing homogeneity of participants and therefore minimizing potential biases. Adult patients with chronic low back pain of at least 3 out of 10 at rest and at least 5 out of 10 under physical strain on the visual analogue scale (VAS) are to be enrolled if conservative treatment, including physiotherapy and adequate pain medication therapy, of at least 3 months failed to improve symptoms according to the multidisciplinary treatment path for chronic back pain of our university hospital. The cause of their symptoms has to be attributable to monosegmental or bisegmental degenerative disc disease or instability, including spondylolisthesis according to Meyerding grade I and II within L2 and S1. Radiographic signs indicative for symptomatic segments concerning degenerative disc disease or instability include spondylolysis, spondylolisthesis, Modic changes, facet joint degeneration, facet joint effusion, spinal stenosis, and severe disc collapse [6].

**Table 1 Tab1:** **Inclusion and exclusion criteria of the study**

**Inclusion criteria**	**Exclusion criteria**
Age of at least 18 years	Previous surgery in the index or adjacent level
Chronic low back pain (visual analogue scale at least 3 out of 10 at rest and at least 5 out of 10 under physical strain) after having failed conservative treatment for at least 3 months	Indication for fusion of more than 2 levels
Indication for monosegmental or bisegmental minimally invasive transforaminal lumbar interbody fusion due to degenerative disc disease or instability, including spondylolisthesis according to Meyerding grade I and II within L2 and S1	Spondylodiscitis, traumatic instability, osteoporotic vertebral body fractures, neoplasm, or spondylolisthesis according to Meyerding grade III and IV of the index level(s)
	Spinal scoliosis with a Cobb angle of more than 10° in the index level(s)

Previous surgery in the index or adjacent level is an exclusion criterion since performing MIS TLIF might be more demanding because of scarring and changes of the individual anatomy. This might significantly increase x-ray exposure and therefore bias radiation exposure between the treatment groups. Likewise, patients showing a spinal scoliosis with a Cobb angle of more than 10° in the index level(s) are to be excluded. Moreover, patients with spondylodiscitis, traumatic instability, osteoporotic vertebral body fractures, neoplasm, or spondylolisthesis according to Meyerding grade III and IV are to be excluded.

### Recruitment procedures

The Department of Neurosurgery of the University Hospital in Freiburg has been performing MIS TLIF procedures routinely for years by using conventional fluoroscopy and 3D fluoroscopy-based navigation. Participants for this study will be recruited primarily from the neurosurgical outpatient clinic. Their eligibility will be proven according to the inclusion/exclusion criteria (Table 1). If eligible, participants are informed about the study protocol. Once written consent is obtained, participants are randomly assigned to one of the two treatment groups (Figure 1).

**Figure 1 Fig1:**
[figure not shown]
**Study design.** The figure shows the process of recruitment, randomization to treatment, and analysis of radiation exposure. FLUORO group, conventional fluoroscopy group; MIS TLIF, minimally invasive transforaminal lumbar interbody fusion; NAV group, three-dimensional fluoroscopy-based navigation group.

### Randomization to treatment groups

Participants will be randomly assigned by using ‘RITA - Randomization In Treatment Arms’ computer software (StatSol, Sereetz, Germany). Participants were randomly assigned in permuted blocks of four and six, according to computer-generated random numbers, to undergo MIS TLIF using either conventional fluoroscopy (FLUORO group) or 3D fluoroscopy-based navigation (NAV group). Separate randomization files are created for monosegmental and bisegmental MIS TLIF. The randomization software ensures that the treatment allocation cannot be viewed prior to randomization and cannot be changed after randomization.

### Study treatments

#### Dosimeter setup

Dosimeters are attached to the surgeon, assistant surgeon, scrub nurse, anesthetist, patient, and C-arm in the operating room (Table 2). Four different types of dosimeters are used (Figure 2). Film dosimeters (AWST-FILM GD 60, *H*_p_(10); Helmholtz Zentrum München, part of the German Research Center for Environmental Health, Personal Monitoring Service, Munich, Germany) are attached to the trunk of the surgeon, assistant surgeon, scrub nurse, anesthetist, patient, and C-arm. Eye lens thermoluminescence dosimeters (EYE-D, *H*_p_(3); Radcard, Krakow, Poland) are attached to the surgeon, assistant surgeon, and scrub nurse. Ring dosimeters (AWST-TL-TD 60, type W; Helmholtz Zentrum München) are tightened around the ring fingers of the surgeon. Moreover, an Electronic Personal Dosimeter (EPD Mk2, *H*_p_(10) mode; Thermo Scientific, Schwerte, Germany) is installed at the flat panel detector of the C-arm to read radiation exposures at predetermined time points during surgery. This dosimeter location approximately corresponds to a surgeon who does not step back from the radiation source when applying x-rays, and this is regularly the case in most operating rooms. With the EPD, we have radiation exposure readings at any time of the operation and thus have the possibility to approximately relate radiation exposures to certain steps of the operation.

**Table 2 Tab2:** **Survey of the intraoperative dosimeter setup**

	**Location**	**Dosimeter type**	**Dosimeter lead protected?**
Surgeon	Left ring finger	Ring dosimeter	Unprotected
	Right ring finger	Ring dosimeter	Unprotected
	Middle forehead	Eye lens dosimeter	Unprotected
	Under lead goggles (left glass)	Eye lens dosimeter	Protected
	Thyroid gland, above lead shield	Film dosimeter	Unprotected
	Thyroid gland, under lead shield	Film dosimeter	Protected
	Left chest, above lead apron	Film dosimeter	Unprotected
	Left chest, under lead apron	Film dosimeter	Protected
	Gonad, under lead apron	Film dosimeter	Protected
	Right knee, under lead apron	Film dosimeter	Protected
	Back, between shoulder blades, above lead apron	Film dosimeter	Unprotected
Assistant surgeon	Middle forehead	Eye lens dosimeter	Unprotected
	Left chest, above lead apron	Film dosimeter	Unprotected
	Left chest, under lead apron	Film dosimeter	Protected
Scrub nurse	Middle forehead	Eye lens dosimeter	Unprotected
	Left chest, above lead apron	Film dosimeter	Unprotected
	Left chest, under lead apron	Film dosimeter	Protected
Anesthetist	Left chest, above lead apron	Film dosimeter	Unprotected
	Left chest, under lead apron	Film dosimeter	Protected
Patient	Thyroid gland	Film dosimeter	Unprotected
	Chest	Film dosimeter	Unprotected
	Gonad	Film dosimeter	Unprotected
C-arm	Next to generator	EPD	Unprotected
	Next to generator	Film dosimeter^a^	Unprotected
	Next to flat panel detector	Film dosimeter^a^	Unprotected

^a^Film dosimeters on the C-arm are removed during the three-dimensional (3D) scan (NAV group, three-dimensional fluoroscopy-based navigation group) since the staff is outside the operating room during the 3D scan. EPD, electronic personal dosimeter.

